## Abstract

**Background:**

The prevalence of hypertension is high and increasing in China in recent years. The treatment and control of hypertension calls for long-term management beyond hospital, which is hard to implement in traditional care settings. Integrated care combined with information technology can promote high-quality healthcare services across the life-course. However, few studies have applied a customized integrated care model in community-based hypertension management in China, catering to the emerging “three-manager” mode. This study aims to identify the effectiveness of a pathway-driven eHealth-based integrated model that implemented as a full-featured telehealth system to facilitate standardized management of hypertension in China.

**Methods:**

The trial has been designed as a 1-year, non-blinded superiority trial with two parallel groups. A total of 402 hypertensive patients who meet the eligibility criteria will be recruited and randomized with a 1:1 allocation. All the participants will receive a mobile device for self-management, which is a part of our telehealth system. Participants in the control group will only use the device for BP measurement and receive regular follow-ups from care providers according to the guidelines. Participants in the intervention group will gain full access to the system and receive intervention based on the proposed model (a well-designed coordinated care pathway consisting of 9 tasks). Outcomes will be measured mainly on three occasions (at inclusion, at 6 months, and at 12 months). The primary outcome is mean change in systolic blood pressure over a 12-month period. Secondary outcomes include changes in diastolic blood pressure, biochemical indexes related to hypertension, lifestyles, self-management adherence, and hypertension awareness, as well as work efficiency of care providers.

**Discussion:**

This study aims to investigate whether a pathway-driven eHealth-based integrated care model based on the “three-manager” mode will improve hypertension control in China. Success of the model would help improve the quality of present community-based management procedures and benefit more patients with uncontrolled hypertension.

**Trial registration:**

Chinese Clinical Trial Registry ChiCTR1900027645. Registered on November 22, 2019.

**Supplementary Information:**

The online version contains supplementary material available at 10.1186/s13063-021-05020-2.

## Administrative information

Note: the numbers in curly brackets in this protocol refer to Additional file 1: SPIRIT checklist item numbers. The order of the items has been modified to group similar items (see http://www.equator-network.org/reporting-guidelines/spirit-2013-statement-defining-standard-protocol-items-for-clinical-trials/).

## Introduction

### Background and rationale {6a}

Hypertension is a major risk factor for cardiovascular disease and affects more than 20% of the adult population in China, according to the latest national survey [1]. The treatment and control of hypertension calls for long-term patient self-management along with supervision and intervention from doctors [2]. However, hypertension management within the traditional care settings is disconnected and time-consuming, which cannot meet long-term care needs of patients [3]. Integrated care is proposed as an approach to transform health services to meet these challenges [4]. In an integrated care setting, health services are delivered by a coordinated multidisciplinary team of providers, aiming to promote the comprehensive delivery of quality services across the life-course [5].

The advent of information technology facilitates the delivery of integrated care services and has demonstrated potential to improve the outcome of hypertension management [6–8]. The importance of information technology in integrated care can be interpreted from different scales. From an individual scale, care planning is a central approach of integrated care, which aims to deliver more personalized and targeted care by creating shared care plans. The care plans clearly articulate the role of each provider and patient in the care process [9]. The use of information technology is considered to be crucial to facilitate the development of shared care plans [4]. From a group scale, the chronic care model (CCM) is one of the most studied integrated care models [10–13]. The key to the success of CCM has proved to be the bidirectional communication within multidisciplinary teams and the provision of continuous self-management support to patients [14]. Information technology plays a key role in achieving the above goals, which has been described as a complete eHealth-based feedback loop in the eHealth Enhanced Chronic Care Model (eCCM) [15]. To conclude, information technology is essential to implement effective integrated care for hypertensive patients.

In China, hypertension management is currently delivered based on communities, mainly conducted by general practitioners (GPs) [16]. In response to the government policy, physicians and case managers (CMs) are gradually participating in the community-based hypertension management to form a coordinated multidisciplinary team called “three-manager” [17]. Similar to other countries, CMs in China are mainly composed of nurses, working under supervision of GPs [18, 19]. Although the “three-manager” mode has been carried out in some provinces, in practice there still exist some problems. One is that current management guidelines do not clearly specify the responsibility of each role in the “three-manager” mode. Another one is that the unbalanced allocation of medical resources in China brings to the difference in abilities of care providers [20, 21]. GPs and CMs in rural areas can hardly perform comprehensive management following the guidelines. These problems result in a significant gap between standards of care and medical practice in hypertension management [22, 23].

### Objectives {7}

To combat the existing challenges of hypertension management in China, we established a pathway-driveneHealth-based integrated care model (PEICM) for the “three-manager” mode, focusing on specifying the responsibility of involved roles and providing a standardized and executable care pathway for long-term management. Based on PEICM, a telehealth system has been designed and implemented. This paper describes a two-arm randomized controlled trial to evaluate the effectiveness of PEICM through the use of the system.

### Trial design {8}

This 1-year study is designed as a randomized, controlled, and non-blinded superiority trial with two parallel groups and repeated measurements at 3 time points (inclusion, at 6 and 12 months). Randomization will be performed as block randomization with a 1:1 allocation. We used the Additional file 1: SPIRIT checklist [24] and the Additional file 2: TIDieR checklist [25] when writing our manuscript.

## Methods: participants, interventions, and outcomes

### Study setting {9}

The trial will be conducted in Yibin city, Sichuan province, China. Yibin is a midsize city located in the joint region of Sichuan, Yunnan, and Guizhou province. Given its population, location, economy, and living standard of people, Yibin can represent the central region of China to a certain extent [26]. Therefore, hypertensive patients in Yibin are representative in terms of demographic characteristics and technology acceptance. In this trial, the participating physicians (cardiologists) are recruited from the First People’s Hospital of Yibin, which is a tertiary hospital with four major districts (A, B, C, and D). A well-equipped health management center (HMC) is established in B district cooperating with ZICT Technology Co., Ltd. (ZICT). The patient enrolment and outcome measurements will be performed in the HMC. The participating GPs and CMs are from 3 community health centers near the First People’s Hospital of Yibin.

### Eligibility criteria {10}

The inclusion criteria are as follows: (1) 18–80 years old, (2) hypertension diagnosis with uncontrolled blood pressure (BP) for at least 1 year, (3) fluent in Mandarin or Sichuan dialect, (4) able to use the system fluently after instruction, (5) mainly visit the hospital where the trial is hold, and (6) have no walking disability. The exclusion criteria are as follows: (1) participate in another trial within 4 weeks before this study, (2) suffer from mental health problems, (3) suffer from cancer and have received chemotherapy or radiotherapy within half a year before this study, (4) suffer from myocardial infarction, (5) suffer from other serious diseases with natural course shorter than 1 year, (6) have no home internet access, and (7) pregnant or prepare for pregnancy.

### Who will take informed consent? {26a}

All patients eligible for the trial will be invited to HMC in B district to attend the enrolment session. CMs will apprise them of the information regarding the study and promise that their personal information will only be accessed by the investigators. The patients who agree to participate in the study will be asked to sign informed consent forms before allocation.

### Additional consent provisions for collection and use of participant data and biological specimens {26b}

The informed consent has included participants’ permission to the collection of blood and urine samples, which will be analyzed in the current study. No ancillary study is planned.

## Interventions

### Explanation for the choice of comparators {6b}

Management guidelines are considered to be the most convincing evidence to guide the management process. The effectiveness of applying the hypertension management guidelines to primary care in China has been tested [27]. Moreover, the care pathway used in our integrated model is mainly extracted from the guidelines. Therefore, we choose guideline-based management as a usual care intervention for the control group.

### Intervention description {11a}

Participants in the control group will receive interventions based on the 2018 Chinese Guidelines for Prevention and Treatment of Hypertension [16]. The guidelines emphasize 4 key components of the management in primary care: hierarchical long-termfollow-up, health education, self-management support, and two-way referral. In this trial, a guideline-based management procedure is as follows: first, patients will be classified into 2 levels according to whether the patients reach target BP, and then, GPs will conduct long-termfollow-up on patients. For level 1 patients, the follow-up frequency is once every 3 months and the follow-up contents focus on complying with current therapy; for level 2 patients, the follow-up frequency is once every 2–4 weeks and the follow-up contents focus on adjusting current therapy to improve BP control. Health education and self-management support will be involved during the follow-up. In addition, a two-way referral channel will be opened to provide further treatment.

Participants in the intervention group will receive interventions based on PEICM, as shown in Fig. 1. The model involves 4 roles in the management: physicians, GPs, CMs, and patients. The responsibility of each role is specified through a well-designed care pathway. The care pathway is initialized based on the guidelines and detailed by several experienced physicians. Nine common tasks are defined in the pathway for hypertension management, which are as follows: diagnosis, risk assessment, hierarchical management, medication guidance, lifestyle guidance, regular follow-up, abnormal condition intervention, health education, and compliance management. The tasks will be generated as executable plans, including doctor intervention plans and patient self-management plans.

**Fig. 1 Fig1:**
[figure not shown]
Diagram of PEICM

The 9 tasks can be grouped into 3 parts: the tasks for regular management, the tasks for pathway variation, and the tasks for self-management. The tasks for regular management include 4 tasks: diagnosis, risk assessment, hierarchical management, and regular follow-up. When a patient is diagnosed with hypertension, he/she will enter the pathway. A cardiovascular risk assessment will firstly be conducted to divide patients into 2 management levels: level 1 for patients in low or middle risk while level 2 for patients in high risk. The management plan for level 1 and level 2 is different. In addition, patients’ risk will be reassessed per week based on their self-monitoring data to dynamically change their management levels. Care providers need to perform regular follow-ups for patients, and the follow-up schedule will also be dynamically adjusted based on the management level. Once a patient is in level 2 for over 3 weeks, a two-way referral channel will be opened. The tasks for pathway variation include 2 tasks: abnormal condition intervention and compliance management. When patients’ self-monitoring data is abnormal, care providers will immediately be informed and conduct the appropriate intervention; when patients’ compliance is low, care providers need to perform an extra follow-up to learn the reason for low compliance and try to improve it. The tasks for self-management include 3 tasks: medication guidance, lifestyle guidance, and health education. Medication guidance aims to provide plans about drug prescription while lifestyle guidance aims to provide plans mainly for diet and physical activity. Health education aims to offer health knowledge to patients, in order to improve their hypertension awareness thus improving their self-management ability.

According to the pathway, the responsibility of each role is specified as follows: physicians are responsible for diagnosis and formulating the self-management plans; GPs are responsible for regular follow-ups, plan adjustment, and abnormal condition intervention; CMs are responsible for health education and compliance management. Patients need to follow self-management plans and perform self-monitoring to receive timely intervention from care providers.

Based on PEICM, a telehealth system has been implemented, which consists of 2 parts: clients for care providers and patients, and a service engine for data storage and pathway execution (Fig. 2). For care providers, the client is in the form of a website that can be accessed on their computers in the hospital. Care providers use the client to supervise patients and conduct the intervention. For patients, the client is in the form of an all-in-one health terminal. The terminal is a combination of an Android tablet with a series of wearable devices (integrating measurement of ECG, heart rate, blood pressure, blood glucose, blood oxygen saturation, and body temperature), which was developed by ZICT (Shenzhen, China). Data measured by the terminal will be automatically uploaded and displayed on the website. In addition, patients can use the tablet to check their self-management plans, read health knowledge, and communicate with care providers. The functional design of the tablet application drew on experience from our previous work [28]. The service engine is a web service deployed on the server, consisting of 4 layers: a data layer, a service layer, a control layer, and an interface layer. The engine will be responsible for saving data from clients and providing decision support based on the pathway.

**Fig. 2 Fig2:**
[figure not shown]
System architecture

In this trial, all the interventions will be conducted through the system. The intervention group will gain full access to the system and manage their hypertension under the guidance of the model. The control group will only gain partial access to the system (only for BP measurement) and receive care as usual. Table 1 summarizes all the interventions for each group.

**Table 1 Tab1:** All the interventions for the 2 groups

Intervention category	Execution method in the control group	Execution method in the intervention group
Diagnosis	By physicians (before the trial)	By physicians (before the trial)
Risk assessment	No execution	Conducted by GPs with the assistance of the system; reassessed based on self-monitoring data per week
Hierarchical management	Executed by the system based on patients’ BP values; only adjusted after regular follow-up; no management plans for patients	Executed by the system based on patients’ risk level per week; provide executable management plans to patients
Regular follow-up	Performed by GPs once every 3 months for level 1 patients and once every 2–4 weeks for level 2 patients; no dynamic adjustment	Performed by GPs once every 3 months for level 1 patients and once every 2 weeks for level 2 patients; dynamically adjusted based on patients’ management level
Abnormal condition intervention	No execution	Conducted by GPs; abnormal condition is informed by the system
Compliance management	No execution	Conducted by CMs; compliance is calculated by the system per week
Medication guidance	Provided by GPs during regular follow-up	Provided by physicians or GPs through the system anytime
Lifestyle guidance	Provided by GPs during regular follow-up	Provided by physicians or GPs through the system anytime
Health education	Provided by GPs during regular follow-up	Conducted by CMs through the system, mainly in the form of online materials

### Criteria for discontinuing or modifying allocated interventions {11b}

The assigned intervention will only be discontinued in response to participant request. No modification of the interventions is planned during the trial.

### Strategies to improve adherence to interventions {11c}

In this trial, adherence to interventions mainly refers to patients’ self-management adherence. For the control group, patients will be reminded to follow their self-management regimes during each regular follow-up. For the intervention group, compliance management is defined as a part of the pathway and patient compliance will be calculated by the system per week based on their self-monitoring data. Care providers will not only remind patients in regular follow-ups, but also perform extra follow-ups to improve low adherence.

### Relevant concomitant care permitted or prohibited during the trial {11d}

No concomitant care or interventions are permitted during the trial.

### Provisions for post-trial care {30}

This is not applicable. No post-trial care is planned.

### Outcomes {12}

The primary outcome of the trial is changes in mean systolic blood pressure (SBP) from baseline (T0) to 12 months (T2). The key secondary outcomes are changes in mean diastolic blood pressure (DBP) and changes in biochemical indexes related to hypertension from T0 to T2. The other secondary outcomes include changes in lifestyles, self-management adherence, and hypertension awareness from T0 to T1 (6 months) and T2. In addition, work efficiency of care providers will be assessed at T2 to validate the model from a care provider perspective.

### Participant timeline {13}

The SPIRIT figure is presented in Fig. 3, which provides an overview of the schedule of enrolment, interventions, and assessments. Figure 4 shows the timeline diagram.

**Fig. 3 Fig3:**
[figure not shown]
SPIRIT figure

**Fig. 4 Fig4:**
[figure not shown]
Timeline diagram

### Sample size {14}

The power calculation is based on the primary outcome measure and aims for a mean systolic blood pressure variation of 5 mmHg with a standard deviation of 16.5 mmHg (the effect size is based on a previous study [29]). Assuming an α of 5%, and power of 0.80, 171 patients per group are required at the end of the trial (342 in total). Considering an attrition percentage of 15%, our aim is to include a minimum of 402 patients at baseline.

### Recruitment {15}

Patients are recruited mainly in 3 ways: (1) review discharged patients’ list of the cardiovascular department, (2) review patient list provided by the medical examination center, and (3) recruit patients through physicians’ social media (for example, the functional module Moments in WeChat). CMs will call the potentially eligible patients to confirm the eligibility, then invite them to attend the enrolment session in HMC.

## Assignment of interventions: allocation

### Sequence generation {16a}

One investigator will generate the randomized allocation sequence using SPSS version 23.0, which allocates 50% of the participants to either group.

### Concealment mechanism {16b}

The allocation sequence is concealed in opaque envelopes from all investigators (except for the investigator who generates the sequence) and care providers until the interventions are assigned.

### Implementation {16c}

All patients who give written consent for participation will be enrolled. CMs will guide the enrolment session. First, each patient will be directed to the baseline assessment, including demographics, basic body measurement, clinical BP measurement, laboratory test, and questionnaires. Then, each patient will be randomly assigned an envelope, inside which is a printed random number with the corresponding group. CMs will open the envelope and find the treatment condition to be conducted for this patient. CMs then give the information about treatment allocation to the patient. After that, each group will be guided to different rooms, and CMs will instruct the use of the system to the control group and intervention group, respectively.

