## Assignment of interventions: blinding

### Who will be blinded {17a}

Due to the nature of the intervention, this study is an open-label trial to all participants and care providers. However, in order to reduce the level of bias, the statisticians involved in the data analysis will be blinded to the group allocation.

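### Assigning envelopes to patients at random conflicts with the declared block randomisation and leaves no defined next envelope to check allocation against

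*Protocol article*

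**What the plan says.** Four sections of the protocol article describe the allocation.

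- Trial design {8}: "Randomization will be performed as block randomization with a 1:1 allocation". No block size is given.
- Sequence generation {16a}: a single investigator produces the list in SPSS, with half of the patients going to each arm.
- Concealment mechanism {16b}: "The allocation sequence is concealed in opaque envelopes from all investigators". The investigator who made the sequence is excepted. Care providers are also kept unaware until assignment.
- Implementation {16c}: after the baseline assessment, "each patient will be randomly assigned an envelope, inside which is a printed random number with the corresponding group". The article goes on to say who unseals it: "CMs will open the envelope and find the treatment condition to be conducted for this patient".

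Three other sections describe the people involved. Under Recruitment {15}, "CMs will call the potentially eligible patients to confirm the eligibility". Under the consent heading {26a}, case managers also inform patients about the study. Under Who will be blinded {17a}, "this study is an open-label trial to all participants and care providers".

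**The concern.** A block sequence balances the arms as patients accrue only if it is used in the order in which it was generated. If each patient receives an envelope by a further random step, that order is replaced by another one, and allocation becomes a draw without replacement from whatever envelopes remain. The method declared in the design section would then not be the one carried out.

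Two separate things are at stake. The first is running balance between the arms, which is what blocking provides. The second is the ability to verify allocation. With ordered use there is always one correct next envelope, and any departure shows as a break in the order. With random assignment, and the number printed inside, nothing visible at enrolment marks which envelope should be used. This matters more here because the trial is open-label and one role has contact with the patient from the eligibility call to the opening of the envelope.

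**Working it through.** **1. The passages side by side.** Trial design {8} and Sequence generation {16a} fix an ordered list. Concealment {16b} puts that list into envelopes. Implementation {16c} links patients to envelopes by a random step and places the random number inside. No section states that envelopes are used in list order. Taken at their word, the design and implementation sections cannot both describe the same procedure.

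**2. The plan's own figure.** Inputs from Sample size {14}: difference 5 mmHg, SD 16.5 mmHg, α 5% (two-sided, from Statistical methods {20a}), power 0.80, attrition 15%.

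- n per arm = 2 × (1.960 + 0.842)² × 16.5² / 5² ≈ 171, as stated.
- 342 / 0.85 = 402.4, against the stated minimum of 402.

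The sample size reproduces. The point does not depend on it, but it supplies the inputs for steps 3 and 5.

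**3. Running balance under a literal draw.** Assumption: a pool of 402 envelopes, 201 per arm. The article gives 402 only as a minimum enrolment and does not mention a pool. After k patients the arm difference has

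SD = 2 × √[k × 0.25 × (402 − k) / 401].

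| k | SD of arm difference | P(absolute difference ≥ 10) |
|---|---|---|
| 50 | 6.6 | 0.17 |
| 100 | 8.7 | 0.30 |
| 200 | 10.0 | 0.37 |
| 300 | 8.7 | 0.30 |
| 402 | 0 | 0 |

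At k = 201 the SD is 2 × √(50.25 × 201 / 401) = 10.0, so a 95% range is about ±20. The difference returns to zero only if every envelope is used.

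**4. Running balance under ordered blocks.** The difference never exceeds half a block. For assumed block sizes of 4, 6 and 8 the maximum is 2, 3 and 4, and simulation of the blocks gave the same values.

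**5. Effect on power.** With 342 analysed patients, SE = 16.5 × √(1/n₁ + 1/n₂):

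- 171/171: power 80.0%
- 181/161 (difference 20): SE 1.79, power 79.9%
- 191/151 (difference 40): SE 1.80, power 79.5%

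Even a large imbalance at the end of the trial costs half a percentage point of power.

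**6. Selection bias.** A figure would need the share of allocations steered and how far steered patients differ in expected SBP change from those they replace. The documents give neither, so no figure is derived.

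**The case against.** The wording may simply be loose. Implementation {16c} does not mention a pool, shuffling or re-drawing, and the phrase could mean only that each patient receives a randomised envelope. This stands as a possibility. If it is right, one sentence settles the matter. The text still needs that sentence, because what it says conflicts with the design section.

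Sealing, outside numbering and an opening log are details that a journal article commonly leaves to the full protocol. That stands too, and their absence is not the finding. The finding rests on a statement the article does make.

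An honest random draw remains a valid randomisation. In an open-label trial it is also less predictable than small blocks used in order. Enrolment is at one centre over about five months, with no interim analysis planned, so temporary imbalance has little consequence. All of this stands, and step 5 of the working agrees.

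Three stronger readings are tempting and are not supported:

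- **That a swapped envelope would leave no trace.** Each envelope carries a printed number from a generated list. If the list is kept, a discarded envelope appears as a number never used. An envelope opened, closed again and returned would be harder to find.
- **That case managers choose the envelope.** The article says they open it. It does not say who selects it, and the sequence is stated to be concealed from care providers until assignment.
- **That the primary contrast is shifted by some number of mmHg.** Any such value would come from invented inputs.

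**Conclusion.** The conflict is real and lies in what the article states: a block sequence is declared, and envelopes are then assigned at random. Read literally, block balance is lost during accrual (SD of the arm difference about 10 at mid-recruitment, assuming 402 envelopes split 201/201), with negligible loss of power and with allocation still random if the draw is honest.

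The point that deserves action is allocation integrity. Without a defined next envelope, one that is set aside or re-picked is harder to detect, in an open-label trial where case managers confirm eligibility, run the enrolment session and open the envelopes. This is a weakness in the safeguard. Nothing in the documents shows that allocation was or will be steered, and the size of any resulting bias cannot be derived from them. The change is worth making because it restores the declared design and strengthens protection against selection bias at almost no cost.

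**What to change.** Reconcile Trial design {8} with Implementation {16c}. In the latter, replace the random assignment of envelopes with wording such as: *each patient is assigned the next sequentially numbered, sealed, opaque envelope, in the order of the generated block sequence.* Then:

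- write the patient ID, date and time on the envelope before it is opened;
- check used envelopes against the generated list at the quarterly audit that the data monitoring committee already carries out;
- keep the block size from the case managers, since ordered blocks are more predictable than a pool draw.

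The baseline assessment already precedes the envelope, so that order needs no change.

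The first participant was enrolled on July 3, 2020, so new wording cannot repair allocations already made. For those patients, reconcile the printed numbers and enrolment dates with the generated list, and report the allocation method actually used.

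The cost is numbering the envelopes, one changed sentence, a line of writing per patient and one more item at an existing audit. No extra staff are needed.
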